### *Inclusion and Exclusion Criteria*

To be eligible for participation in this study, individuals must meet the following criteria: 1) HIV-positive diagnosis confirmed through testing in our study; 2) time since first notification of HIV-positive status less than 30 days prior to interview; 3) *able and willing to bring in an injecting network member for screening*; 4) being male; 5) 18 years of age or older; 6) had sex in the previous 6 months; 7) injected drugs in the previous 6 months; and 8) planned residence in Thai Nguyen for the next 24 months.

Exclusion criteria: 1) is unwilling to provide locator information; 2) is unable to participate in the group due to psychological disturbance, cognitive impairment or threatening behavior; or 3) is currently participating in other HIV or drug use intervention activities. At the screening visit, we will ask a series of questions about whether the participant has been previously tested for HIV, the approximate dates of the tests, and result of the most recent test. We will exclude females in this study because 97% of IDUs in Thai Nguyen are male and the vast majority of females who inject drugs are sex workers and would require a different intervention to address their unique risk factors. We will recruit newly diagnosed HIV-positive IDUs since IDUs who have known their status for a long time may differ in their mental and physical states than those who have just learned their diagnosis.

As part of the screening interview, index participants will be asked to provide a list of 10 names of their injecting networks. A network inventory will be performed shortly after the screening interview to identify the first three peers listed that meet the following network enrollment criteria: 1) injected or shared drug paraphernalia with index in the past 6 months; and 2) interacts at least once a week with the index. In order to participate in the intervention component of the study, the index will be required to bring an eligible injecting network member into the study. The index participant may either accompany a network member to the study site or provide them with a sealed envelope containing information about the study. Network members who present for screening will be verified through a database of names provided by index participants. Those who decide to continue with the study will be screened: Eligibility criteria for network members: 1) HIV-negative; 2) 18 years or older; 3) injected or shared drug paraphernalia with index in past 6 months; and 4) interacts at least once a week with index. Exclusion criteria: 1) unwilling to provide locator information; 2) has psychological or cognitive impairment; or 3) currently participating in other HIV interventions. Study staff will further describe study objectives, procedures, risks and benefits to eligible participants, and answer any questions. Informed consent will be obtained, and a study network participant card issued.

### *Gender, Age and Locale*

We will exclude females in this study because 97% of IDUs in Thai Nguyen are male and the vast majority of females who inject drugs are sex workers and would require a different intervention to address their unique risks. We've restricted participation to those 18 years and older because under Vietnamese regulations, individuals 18 years and older can independently consent to participate in a research study without the consent of a parent.

Assessment and intervention sites are in separate locations a mile from each other within Thai Nguyen City to ensure that the assessment team is blinded to participants' intervention assignments. The assessment facility consists of 2 buildings with 7 private, soundproof rooms. Separate rooms are used to receive participants, administer interviews, and to conduct HIV counseling and to collect specimens. Every effort is made to ensure that both facilities are as anonymous as possible (e.g., no signs outside identifying the building), in order to protect participant confidentiality.

### **Procedures:**

#### **Phase I: Formative**

##### *Recruitment Process:*

Participants for in-depth interviews will be identified using purposive sampling. Specifically, we will select 12 HIV-positive IDUs who have disclosed their HIV status to at least one person and 12 HIV positive IDUs who have not disclosed to anyone from HIV-positive IDUs who were screened in our previous study but were not enrolled due to their HIV seropositive status and who had indicated their willingness to be contacted for future studies (n ~ 280). We are purposively sampling IDUs who have known their status for 1 year in order to understand the initial impact of the HIV diagnosis on their mental health and injecting and sexual behaviors. We will also purposively sample HIV-positive IDUs for piloting our assessment measures and individual-level intervention components. The two women and two men of unknown HIV or drug using status will be recruited from the general community by the health staff in Thai Nguyen.

We will recruit 10 female partners for in-depth interviews through volunteer self referrals from male participants. Ethnographers will ask IDUs who report that they have shared their HIV test results with their partner whether they would be willing to refer their partner for an interview.

For focus group discussions about community attitudes and behaviors and piloting of community-level intervention components, we will recruit men and women of unknown HIV or drug using status from the general community through the community health staff in Thai Nguyen.

Interviewers will read and explain the informed consent process to eligible participants, and if the participant agrees, written consent will be obtained and documented. All subjects will be given a copy of the form. All project activities will occur in a private project facility in Thai Nguyen. To reimburse participants for their time, participants will be given the Vietnamese Dong equivalent of \$6.50 for in-depth interviews and \$6.50 for focus group discussions.

##### *Study Procedures:*

**In-depth Interviews:** Total participants will include 24 HIV-positive IDUs who have known their status for 1 year, 12 of whom have disclosed their status to at least one person, and 12 of whom who have not disclosed their status to anyone, as 10 female partners of HIV-positive IDUs. In depth interviews of HIV-positive IDUs who focus on how participants learned of their HIV-status, and their experiences with stigma, the extent and nature of their social support networks as well as their injecting and sexual risk practices over the past year. Ten in-depth interviews with female partners of HIV-positive IDUs will focus on the women's experience

with their partner's HIV serostatus disclosure. Interviews will be tape-recorded and will last approximately 1 hour. The four men and women of unknown status that will be interviewed will be asked similar questions to the formative phase focus group participants described below, including questions about community attitudes towards PLWH, towards the Women's Union and towards the Youth Union. The Women's Union and Youth Union are non-governmental voluntary grassroots organizations established in the early 1930s at national, provincial, district, and village levels. Selected members will be trained as community mobilization volunteers.

Focus Group Discussions: Approximately 110 focus group participants will be recruited (2 groups of 15 participants, and 10 groups of 6-8 participants). The focus groups will identify norms surrounding HIV-related stigma and attitudes towards the Women's Union and Youth Union as well as to pilot intervention components. Each focus group discussion will be tape recorded and last approximately 1 hour.

Pilot of Assessment Measures: We have developed an assessment battery from a variety of studies that will be piloted with 20 HIV-positive IDUs. We will use the iterative continuous quality improvement strategy to pilot and receive information feedback for each of the following measures: sexual HIV risk behaviors, drug related HIV risk behaviors, stigma, mental health disclosure of HIV-status, partner uptake of HIV Voluntary counseling and testing, social support, and self-reported disease status. Each participant will be asked for feedback about the procedures the assessment measures, and their reaction to having such questions asked of them. These sessions will last approximately 1 hour.

## **Phases II-IV: Baseline, Intervention and Evaluation**

### *Recruitment Process:*

For recruitment into our randomized trial, we will expand our recruitment strategy from our experimental intervention among HIV-negative IDUs in Thai Nguyen. (IRB protocol # H34.01.09.04A1) Our recruitment efforts will continue with the same network of former and current users as recruiters (n = 31). Recruiters will be paid a salary, rather than an amount per participant recruited, to ensure a non-coercive environment. Training workshops will emphasize the importance of voluntary participation and supervisors will briefly interview 5% of participants at the study site to ensure that their decision to participate was completely voluntarily. Using a snowball sampling technique, recruiters will approach their current or former drug networks in a private place and distribute brochures and answer questions about our study. They will then accompany or refer subjects that are interested in participating to the study site in order to be screened. In order to maintain confidentiality of participants, HIV status as an eligibility criterion will not be revealed to outreach workers. During meetings with counselors at VCT centers in the province, the study will be described and counselors will be asked to distribute printed brochures that describe the study. Mass publicity campaigns are not planned to avoid adverse public attention toward the study which would undermine recruitment efforts and jeopardize the study.

Index Participants: Potential participants who come to the study site will be greeted by project staff and provided detailed information about the project, including study objectives, procedures, potential risks and benefits to the potential participant. Those who decide to continue with the study will be screened for eligibility and exclusion criteria. To establish eligibility, interviewees will obtain informed consent and administer a 15-minute screening questionnaire. As part of the screening interview, participants will be asked to provide a list of 10 names of their injecting networks. Additionally, the index participant must either accompany a network member to the study site or provide them with a sealed envelope containing information about the study in order to participate in the study.

Injecting Network Participants: A network inventory will be performed shortly after the screening interview of each index participant to identify the first three peers listed that meet our network participant enrollment criteria. Network members will be greeted by study staff upon arrival to the study site, and will be verified

through a database of names provided by index participants. Those who decide to continue with the study will be screened, and study staff will further describe study objective, procedures, risk and benefits to eligible participants and obtain written informed consent.

In-Depth Interviews: We will be conducting 10 in-depth interviews at each follow-up visit among Index participants who are randomized to the intervention arm and who return for their follow-up assessment. Survey interviewers will ask every 10th participant to participate in an additional interview until we have recruited 10 participants. We will also conduct brief qualitative interviews among a cohort of 3 community members in all villages every 8 months. Potential participants will be introduced to the study through the community health station staff in Thai Nguyen. These informants will be purposively selected to include men and women who are married and unmarried with different levels of education and types of employment.

Tracing Procedures: At enrollment, screeners will document the subjects' name, telephone number if available, typical sleeping location and names of contact who usually know where to find the subjects with the promise of confidentiality to not reveal the subject's involvement in the study. Subjects will be given an appointment for their next follow-up visit at each assessment visit and will be reminded during sessions of their next appointment. We have implemented a well-designed computerized follow-up program to keep track of all scheduled daily appointments and missed appointments together with contact information. If the participant is in the provincial rehabilitation center or hospital, we will conduct the follow-up visit in a private room at the center. As in our previous HIV-negative study, participants who become incarcerated will be followed up at home when released.

#### *Study Procedures:*

Pre-Screening Assessment: After informed consent is obtained, trained interviewers will administer a brief face-to-face questionnaire. The questionnaire will contain approximately 10 questions and will take approximately 5 minutes to complete. Categories of questions include demographics, injecting and sexual history and practices, injecting networks and locator information. We will test HIV among both index IDUs (HIV-positive) and their injecting partners (HIV-negative) to assess eligibility for participating in the study. We will use the WHO/CDC Protocol for VCT at project facilities. Trained counselors will perform risk assessment and explain the meaning of test results. Participants will provide blood from a finger prick and 2 rapid EIA tests will be run simultaneously. Results will be provided at the screening visit, and HIV posttest counseling will be provided according to WHO/CDC protocols. The staff physician will be consulted if other health problems are identified and active referrals for medical care will be provided as needed. Additionally, we will offer clinical care for the diagnosis and treatment for opportunistic infections that may be related to HIV at no cost to our participants. In order for individuals to process the results of their HIV test, study enrollment will occur at a later visit; individuals who meet the study criteria will be contacted one week later and invited to return for an enrollment and baseline survey visit.

A copy of the screening questionnaire will be forwarded for IRB approval.

Baseline and Follow-up Assessments: After informed consent is obtained, a questionnaire will be administered to all participants at enrollment. Follow-up questionnaires will be conducted among all Index participants at months 3, 6, 12, 18 and 24, and among Network participants at month 24. Follow-up questionnaires will be conducted among all network participants at month 24. The questionnaire will be administered through face-to-face interviews in a private room at the project facility with trained interviewers. and will take approximately 1 hour to complete. Participants who appear influenced by drugs or otherwise not lucid will be asked to return for an interview the next day. Categories of questions include: Demographics, sexual risk behaviors, injecting behaviors, stigma, coping with HIV/AIDS, depression and other mental health issues, disclosure of HIV status, partner uptake of HIV VCT, social support, correct condom use and stage of disease. At baseline and each follow-up visit, Index participants will be asked to provide blood specimens in order to assess the stage of their HIV disease. Trained phlebotomists will take approximately 10cc of blood. Samples will be kept in mobile coolers labeled with the participant's study number and transferred to Hanoi Medical School for flow cytometry for CD4+ counts. Since HIV testing is part of our pre-screening

assessment, HIV tests will only be conducted among Network participants at month 24. As in the pre-screening assessment, participants being tested for HIV will be asked to provide blood through a finger prick.

A copy of baseline and follow-up questionnaires will be forwarded for IRB approval.

In-Depth Interviews: Qualitative interviews among 10 participants at each follow-up visit and among 3 community members every 8 months will be administered by trained interviewers after informed consent is obtained. All interviews will be tape recorded and will last approximately 1 hour.

#### *Intervention Procedures:*

Individual level posttest counseling and support groups for HIV-positive IDUs: The individual level intervention consists of a sequence of posttest counseling and support group sessions that builds on an overall staged, sequential approach to behavioral change for HIV-positive IDUs. Posttest counseling will focus on coping and disclosure. Support groups sessions will focus on HIV knowledge and skill-building while simultaneously providing social support through shared experiences of being an HIV-positive IDU. Each participant in the intervention arm will participate in two 2-hour individual posttest counseling sessions and *three* 2-hour support group meetings consisting of 6-10 participants. Support group meetings will be conducted by a team of two facilitators; counseling sessions will be conducted by one of these same facilitators.

Structural level community-based stigma reduction programs: Stigma reduction programs will begin in a village randomized to the stigma reduction arm within a week of village randomization and will continue throughout the 24 months of the trial. Programs will aim to reduce perceived community HIV stigma among HIV-positive IDUs. Our objectives are to correct misconceptions about HIV transmission; de-link PLWH from “social evils”; and promote positive messages on HIV and PLWH in the community. This will be achieved by promoting messages on video, providing opportunities for community members to interact directly with HIV infected IDUs while providing a meal service, and through opportunities for community members to engage in dialogues with community mobilization volunteers. The volunteers, acting as change agents, provide the link among the different programs. First, video presentations will feature 2 videos that challenge common misunderstandings about HIV transmission and promote positive messages on HIV-positive individuals. Each video presentation will be followed by a question-answer session on HIV/AIDS with a community mobilization volunteer. Second, meals on motorcycles (MOM) will enable community members to act on the videos’ messages by facilitating interaction between PLWH and community members. While mobilizing the community to contribute food and meals, community mobilization volunteers will simultaneously engage in discussions about HIV/AIDS with community members. The two programs will be supplemented by community outreach. Three teams of community mobilization volunteers will disseminate HIV/AIDS information and answer questions through one-on-one or group discussions in the community as part of the effort to actively promote videos and MOM. All programs will be publicized through weekly public loudspeaker announcements.

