##### **Phase II-IV: Baseline, Intervention and Evaluation**

To determine the effects of combined and separate individual and structural level activities on injecting and sexual behaviors, a four arm randomized intervention trial will be conducted. Two villages will be randomly selected from each of the 4 districts in Thai Nguyen with the largest numbers of IDUs. Within each district, one village will be randomly assigned to receive the stigma reduction programs and the other to receive the control, and within each village (regardless of stigma reduction assignment) a random half of the Index IDUs will be assigned to the intervention (enhanced posttest counseling and skill building support groups) and the other half to the control. The overall study design is shown below in Figure 1. The primary outcomes among

Index participants will be drug-related and sexual risk behaviors. The primary outcome among Network participants will be HIV incidence. The intermediate outcomes will include perceived stigma, correct condom use, partner uptake of HIV VCT, perceived social support, depression, and self-reported disclosure.

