#### **Phase II-IV: Baseline, Intervention and Evaluation**

#### *Sample Size and Power Calculations*

For our primary hypothesis, that Index IDUs assigned the individual and structural level interventions will have decreased frequency of sexual and injecting risk behaviors, a total sample size of 404 HIV-positive IDUs enables us to detect a 40% or 50% decrease in sexual and injection risks, accounting for a 20% drop-out rate. Power calculations assumed intention-to-treat distributions, 85% power and an alpha of .05. With a sample size of 404, we can detect decrease in frequency of unprotected sex of .40 or above (assuming the stigma reduction programs are as effective as the individual-level intervention; .50 or above if it's 50% as effective) for analyses on IDUs. If the variance covariance parameters are similar between the sexual and drug risk trajectories, we can also detect an increase in frequency of using new needles and syringes of .40 or above for analyses on IDUs.

For our secondary hypothesis, that network members of IDUs assigned the individual and structural level interventions will have decreased HIV incidence, we estimate that a sample size of 400 (200 combined sample size for the arm receiving both interventions and the arm receiving both controls) HIV-negative network members will enable us to assess differences in HIV incidence among the HIV-negative injecting network members of HIV-positive IDUs, accounting for a 20% drop-out rate ( $160 \times 2 / (1 - 20/100)$ ). With 80% power and alpha of .05, we can detect a decrease in 24-month HIV incidence of between 20 -25% or more for analyses on injecting network members.

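### The 85% power for 404 index men reports an allowance for drop-out only, although about half of them receive their intervention in support groups of 6-10 whose outcomes may be correlated

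*Protocol*

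**What the plan says.** **Allocation.** Under Study Design and Rationale (Phase II-IV), within each village "a random half of the Index IDUs will be assigned to the intervention". That is about 202 of 404 men, in arms 2 and 4 of the four listed under Aims.

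**Delivery.** Under Intervention Procedures, each of these men has two individual counseling sessions and three "2-hour support group meetings consisting of 6-10 participants". Two facilitators lead each group, and one of them also gives the counseling.

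**Power.** Under Sample Size and Power Calculations (Phase II-IV), "a total sample size of 404 HIV-positive IDUs enables us to detect a 40% or 50% decrease in sexual and injection risks". The section adds: "Power calculations assumed intention-to-treat distributions, 85% power and an alpha of .05". The only inflation it reports is "accounting for a 20% drop-out rate". The only reference to a variance structure is conditional: "If the variance covariance parameters are similar between the sexual and drug risk trajectories". That wording concerns repeated measurements on a man over follow-up. It does not concern correlation between men who share a group.

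**The concern.** Men who meet in the same small group, under the same two facilitators, are likely to have outcomes more alike than men from different groups. Here that is close to the intended mechanism, because the sessions are meant to give social support through shared experience. Positive correlation enlarges the variance of the mean in a grouped arm, so a calculation for independent men overstates power.

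The primary hypothesis concerns men who receive both interventions, so the arm that matters most is a grouped one. An allowance for villages would not cover this. The within-village comparison of men with and without the individual-level intervention largely removes village effects but keeps support-group effects.

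**Working it through.** **Inputs from the protocol.** N = 404; drop-out 20%; power 85%; alpha .05 (sidedness not stated, two-sided assumed); effect .40, or .50 if the stigma programs are half as effective; one half allocated to the individual-level intervention; group size 6-10 (midpoint 8). The number of groups follows: 202/10 = 20.2 to 202/6 = 33.7, so about 20 to 34.

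**Inputs not given.** Group ICC, baseline frequency, SD, covariance values and the contrast powered. The ICC is therefore assumed, at .01, .05 and .10.

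**Step 1: the stated figure.** The drop-out step is consistent: 404 × 0.8 = 323.2 evaluable men, or 80.8 per arm, and 323/0.8 rounds up to 404. The 85% itself cannot be reproduced.

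Reading .40 as a standardized difference, two-sided:
- Arm against arm: Φ(.40 × √(80.8/2) − 1.960) = Φ(0.58) = 72.0%.
- One arm against the other three: Φ(.40 × √60.6 − 1.960) = Φ(1.15) = 87.6%.
- Factorial margins: Φ(.40 × √(161.6/2) − 1.960) = Φ(1.64) = 94.9%.

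Reading .50 the same way, arm against arm gives 88.8%. Reading .40 as a relative fall in a proportion, the answer depends on the unstated baseline: arm against arm, 58.8% at a baseline of .40 and 87.0% at .60. The 85% is therefore taken as given, as the power without clustering.

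**Step 2: allowance for groups on one side.** With stable groups of size m formed within one arm, the variance of that arm's mean is multiplied by 1 + (m − 1) × ICC. In an equal contrast with an ungrouped arm, the variance of the difference is multiplied by

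F = 1 + (m − 1) × ICC / 2,

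and power = Φ[(1.960 + 1.036)/√F − 1.960].

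With m = 8:

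| ICC (assumed) | F | Power | N to keep 85% (404 × F) |
|---|---|---|---|
| .01 | 1.035 | 83.8% | 419 |
| .05 | 1.175 | 78.9% | 475 |
| .10 | 1.350 | 73.2% | 546 |

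Worked line for ICC .05: 2.996/√1.175 = 2.764; 2.764 − 1.960 = 0.804; Φ(0.804) = 78.9%.

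**Step 3: sensitivity to group size.** At ICC .05, power is 80.6% with m = 6 and 77.3% with m = 10. At ICC .10 it is 76.4% and 70.1%. If the 20% drop-out also thins the groups, m = 8 × 0.8 = 6.4 and power is 84.1%, 80.3% and 75.8% at ICC .01, .05 and .10.

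**Step 4: if both sides meet in groups.** F becomes 1 + (m − 1) × ICC. With m = 8 this is 1.07, 1.35 and 1.70, giving power of 82.6%, 73.2% and Φ(2.996/1.304 − 1.960) = Φ(0.338) = 63%.

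**The case against.** **The calculation may already contain a clustering term.** The reference to variance and covariance parameters shows that a model lay behind the summary, and the summary does not claim to be complete. This stands in part. A reader might infer that clustering was ignored, but the protocol shows only that no allowance is reported.

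**The control may also meet in groups.** Aims calls arm 1 attention-controlled, and no section describes what the control men receive. A reader might infer that controls are ungrouped, but the protocol does not say so. This stands, and the one-sided figures depend on it. Grouped controls would make the loss larger (step 4).

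**Groups may not be stable.** The protocol does not say that the same men meet all three times, or that a group is drawn from a single arm. If membership changes or arms mix, the simple design effect does not apply directly.

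**The size is not anchored.** The 85% cannot be reproduced, every ICC is assumed, and a single-endpoint formula is applied to outcomes followed at five visits. The one-sided factor does not fit arm 4 against arm 2, or one arm against three. All of this stands. Power near 70% needs both an ICC of .10 and groups of 10, and the protocol supports neither.

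**The analysis belongs to the SAP.** This stands for the model. A reader might infer that men in a group will be analysed as independent, but the protocol states no analysis model for index outcomes. It does not dispose of the power figure, which the protocol itself states next to a grouped delivery that it also fixes.

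**Conclusion.** The point holds as a limited one about the stated power. The protocol claims 85% and reports an allowance for drop-out alone, while about half the men receive a group-delivered intervention. Any positive within-group correlation puts the power below the claim.

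For a grouped arm against an ungrouped arm, across group sizes of 6 to 10, the loss is about 1-2 points at ICC .01, about 4-8 at .05 and about 9-15 at .10. These figures rest on four assumptions: 85% is the power without clustering, the test is two-sided, groups are stable and within one arm, and the ICC is as assumed. If the true ICC is small, so is the loss.

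The figures should not be read as the trial's actual power, or as applying to every contrast that involves a grouped arm. They also leave out villages: the stigma programs are allocated to 8 villages of about 50 index men each (404/8 = 50.5). That is a separate and probably larger source of clustering, so correcting for support groups alone would not give a valid power figure.

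**What to change.** In Sample Size and Power Calculations:
- State the assumed support-group ICC and the mean group size, and say whether drop-out is taken to shrink the groups.
- Restate the power, or the detectable difference at 404 men, with a partially nested allowance for the arms that meet in groups. Present it alongside any village allowance.
- Say what the attention control consists of. If control men also meet in groups, apply the allowance to both sides.
- If a clustering term was already included, report its value. That settles the point.

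Separately, confirm that support-group membership is recorded for each man. Study Design and Rationale mentions session log forms but does not say that they identify the group. How the analysis uses that membership is for the SAP.

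The cost is a few sentences, probably a lower stated power, and one data item if group membership is not yet captured. Nothing in the delivery of the intervention changes. Keeping 85% by enlarging the trial would take the 419, 475 or 546 men shown above, but restating the power is enough to correct the text.
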